***Inclusion Criteria:***

- 30-49 years
- HPV-positive
- Attending the cervical cancer screening program conducted by the Saint-Damien Health-Care Centre
- Understands study procedures and accepts voluntarily to participate by signing the informed consent form (ICF)

***Exclusion Criteria:***

- Previous Hysterectomy
- Conditions that can interfere with visualization of the cervix
- Pregnancy > 20 weeks
- Not able to comply with protocol study.

***Study design:***

This cohort study will be carried out in the Saint-Damien Health-Care Centre, in Ambanja, Madagascar. Women meeting the inclusion criteria will be invited to participate to the study after informed consent. Recruitment will be made during the month of July 2014.

***Study procedure:***

An informed consent form will be obtained from each woman prior to participation in the study. A questionnaire will then be filled out, assessing socio-demographic data and clinical information. These questionnaires will be available in a secured online platform containing all data from all participants. This platform will be network connected with the University Hospitals of Geneva.

A trained on-site expert will visualize the cervix with a vaginal speculum and then acetic acid 5% will be applied for at least 30 seconds. Then, a conventional VIA is performed.

In addition, acquisition of an additional set of photography of the cervix than that routinely obtained during the exam (with a digital camera or a colposcope) will be performed. The additional digital images will be obtained with a Smartphone (Samsung Galaxy S5). Photographs will be done before and after application of acetic acid and Lugol. This will result in approximately three photos per woman and should yield very little discomfort for the women.

A university-based on-site expert will independently conduct another VIA evaluation, blinded to the health worker’s evaluation.

Biopsies of the cervix (on the four forties and the lesion if any) and endocervical curettage will be performed.

All photographs will be transmitted to University Hospitals of Geneva for expert analysis. This will be made by MMS, e-mail or via RAFT network. All the images will be stored in the online platform.

The “offsite” diagnosis will be transmitted to health care worker having conducted the “in-site” diagnosis and consensus will be discussed.

The on-site health worker and the on-site university-based expert will evaluate the stored digital images (D-VIA) three months after the initial visit, and blinded to their original evaluation.

Since correlation between cytology and histology is known to be poor ([4](#_ENREF_4)), a cervical smear will be done at the end of the procedure.

Subjects deemed to be VIA positive will be treated at the same visit with cold coagulation if eligible (see flowchart).

All photographs stored in the database will be later used for educational purposes.

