**Abstract**

**Background:** Cervical cancer is the leading cause of cancer death in females in Madagascar. In this country, a large-scale screening of precancerous lesions with cytology is hardly possible, because of the lack of specialists and infrastructures. Visual inspection of the cervix with application of 5% acetic acid (VIA) is an inexpensive alternative but very subjective since it depends on the examiner’s experience. Mobile telemedicine is a very promising tool in order to assist non-expert health-care workers in rural area for cervical cancer screening.

**Objective:** To assess if Smartphone may assist health-care worker (on-site) and to evaluate the diagnostic reliability and accuracy of cervical examination with smartphone photos of VIA (D-VIA) compared with conventional VIA, for women testing positive for human papillomavirus (HPV).

**Material and method:** On-site health care workers will be trained in VIA. Prescreened HPV-positive women will be referred to VIA evaluation, during which digital images with a smartphone (D-VIA) will be taken for later evaluation by a VIA specialist in Geneva linked by telemedicine. Women with positive VIA results will be treated with cold coagulation if eligible. Histological results will be considered as gold standard. The results will be analyzed with Cohen’s kappa coefficient, Mcnemar’s test and Bonferroni’s adjustment for multiple comparisons to assess the performance of D-VIA.

**Expected results:** Based on the results of this project, we will develop an educational training and quality assurance program for health providers for VIA and so contribute to a scaling-up of cervical cancer control. An appropriate triage by VIA will reduce not only an excessive referral rate but also an excessive treatment delay, giving the possibility of a “screen (HPV), see (VIA/D-VIA), and treat” program in a single or two visits.

**Key words:** Cervical cancer; HPV; VIA; screening; smartphone; telemedicine

1. **Introduction**

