Primary outcomes:

1) To evaluate if a Smartphone may assist health-care worker (in-site) for cervical cancer screening;

2) To evaluate how the expert at a distant location (off-site) may improve VIA results.

Secondary outcomes:

1) To assess the agreement between diagnoses based on the visualization of the cervix with the unaided eye, after the application of 5% acetic acid (control) during a patient clinical consultation and diagnoses for the same patient based on evaluation of Smartphone photos.

1. **Material and method**

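### D-VIA readers are given a Lugol photograph while the VIA comparator rests on acetic acid alone, so VIA v D-VIA differences mix medium and stain (firm for comparisons 1 and 4, conditional for 2 and 5)

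*Protocol*

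**What the plan says.** **Comparator.** The protocol's Objective section (secondary outcomes) defines the control as "visualization of the cervix with the unaided eye, after the application of 5% acetic acid (control)". The Study procedure agrees: acetic acid is applied, and a conventional VIA follows. No unaided-eye Lugol reading is described anywhere.

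**Index test.** The Abstract describes D-VIA as "cervical examination with smartphone photos of VIA (D-VIA) compared with conventional VIA". The Study procedure sets out the smartphone pictures: "Photographs will be done before and after application of acetic acid and Lugol". It adds: "This will result in approximately three photos per woman".

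**Who sees which pictures.** For the distant reader: "All photographs will be transmitted to University Hospitals of Geneva for expert analysis". For storage: "All the images will be stored in the online platform". Of the on-site health worker and the on-site expert, it says that they "will evaluate the stored digital images (D-VIA) three months after the initial visit". No sentence restricts a D-VIA reading to some of the photographs, fixes the order in which they are opened, or asks for a result before the Lugol picture is seen.

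**Use of the readings.** The Statistical analysis section lists eight pairwise agreement comparisons, assumes 8% CIN2+ detection by D-VIA against 4% by VIA, and plans accuracy figures for the smartphone diagnosis against histology.

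**The concern.** A comparison of VIA with photographs of VIA should change one thing, the medium. As the procedure stands, D-VIA readers also have a picture with a second stain that the VIA reading did not use. If D-VIA finds more lesions, has lower specificity or agrees poorly with VIA, the cause could be the photograph or the Lugol image. The direction is open, since a Lugol picture might add true or false positives.

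This has to be settled before the readings begin. If a reader records one result from the whole photo set, no later analysis can recover what that reader would have concluded from the acetic-acid picture alone. A statistical analysis plan cannot repair that.

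**Working it through.** **1. The two tests side by side**

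| | Conventional VIA | D-VIA as written |
|---|---|---|
| Medium | Unaided eye | Smartphone photographs |
| Stain available | 5% acetic acid | Acetic acid and Lugol |
| Source | Objective; Study procedure | Study procedure |

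One native, one acetic-acid and one Lugol picture make 1 + 1 + 1 = 3, which fits the protocol's figure of about three per woman. The native picture adds no contrast, because the examiner also sees the cervix before acetic acid.

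**2. What changes within each listed comparison**

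I take the first live VIA to be the health worker's, since the university expert's VIA is blinded to the health worker's evaluation. The text places that first VIA directly after acetic acid. It describes the expert's VIA after the photographs and does not say whether Lugol is already on the cervix.

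| Comparison | Reader changes | Medium changes | Stain changes |
|---|---|---|---|
| 1. Health worker VIA v distant D-VIA | yes | yes | yes |
| 2. On-site expert VIA v distant D-VIA | yes | yes | depends on order |
| 3. Health worker VIA v on-site expert VIA | yes | no | no D-VIA reading; outside this point |
| 4. Health worker VIA v own D-VIA | no | yes | yes |
| 5. On-site expert VIA v own D-VIA | no | yes | depends on order |
| 6, 7, 8. D-VIA v D-VIA | yes | no | no, same photo set |

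Comparisons 4 and 5 hold the reader constant, so they are the ones that could isolate the photograph. In 4 the stain certainly changes with it; in 5 it may.

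**3. Can the planned data separate the two?**

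Write the difference in positivity, as a simple additive shorthand, as:

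- Comparison 4: medium + stain
- Comparison 1: medium + stain + reader

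Subtracting 4 from 1 leaves the reader term, which is what comparison 7 already gives. Medium and stain appear only as a sum. No planned reading uses the acetic-acid photographs alone, and no live reading with Lugol is defined.

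**4. The plan's own figures**

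The assumed gain is 8% − 4% = 4 points, or 40 per 1000 women. For two independent groups, two-sided 0.05 and 80% power, the usual formula gives 553 per group, or 1106 in total, so the stated 1000 is not reproduced that way. That is a separate matter. The design is paired, for which

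n = (z₀.₉₇₅√ψ + z₀.₈₀√(ψ − d²))² / d²,

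with d the difference and ψ the discordant proportion, which the protocol does not give. Its range is:

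- ψ = 0.04 (no woman positive on VIA only): (1.960 × 0.2000 + 0.842 × 0.1960)² / 0.0016, giving 194 women.
- ψ = 0.12 (no woman positive on both): (1.960 × 0.3464 + 0.842 × 0.3441)² / 0.0016, giving 587 women.

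With 1000 pairs and ψ = 0.12, power is Φ((0.04 × √1000 − 1.960 × 0.3464) / 0.3441) = Φ(1.70) ≈ 96%; it is higher for smaller ψ. The planned test is therefore well powered at 0.05 for the 4-point contrast. What is unclear is what that contrast measures.

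**The case against.** **Access is not use.** The protocol shows that D-VIA readers receive the Lugol picture. It does not say that a positive result may rest on it, and the Abstract's description of D-VIA points to acetic-acid images. A reading manual might settle this. This stands as a reason for moderate confidence. It does not remove the point: the procedure sends, stores and scores the images without restriction, and if acetic-acid images alone were meant, the sentence saying so is still needed.

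**The whole package may be the question.** The primary outcomes ask whether a smartphone assists the health worker and how a distant expert improves VIA. A photo set with Lugol can answer that, and the secondary outcome speaks of smartphone photos without naming a stain. This stands in part. It is why the combined reading should be kept, and why this is an improvement and not a fatal defect.

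**Stronger readings that the documents do not support.**

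- *That all four VIA v D-VIA comparisons are certainly affected.* If the on-site expert's live VIA follows Lugol, the stain contrast in 2 and 5 shrinks or disappears.
- *That the accuracy figures are invalid.* Set against histology, they are valid for the image set read. The issue is what they are called.
- *That a known part of the 4-point gain, and so of the power, belongs to Lugol.* No figure for a Lugol share is given, and confounding is not loss of power. The 8% comes from previous studies whose photo set is not described, so it may already include Lugol. Any table of power by assumed Lugol share would be illustration only.

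**Conclusion.** The point holds within limits. As written, D-VIA differs from VIA in medium and in the stain available to the reader, and the planned readings cannot separate them. This is firm for 2 of the 8 comparisons (1 and 4), with a change of reader as well in 1. It is conditional for 2 more (2 and 5), on an order that the protocol leaves unstated. Comparisons 6, 7 and 8 are unaffected.

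D-VIA sensitivity, specificity and predictive values describe acetic acid plus Lugol photographs, not smartphone photographs of VIA as the Abstract has it. The size and direction of any Lugol effect are unknown. The conclusion assumes that D-VIA readers use the pictures they are given and that no reading rule outside the protocol says otherwise. It should be fixed; confidence is moderate.

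**What to change.** In the Study procedure, define D-VIA, for the eight comparisons and the accuracy analysis, as the reading of the native and acetic-acid photographs. Each D-VIA reader, distant or at three months, records and locks that result before the Lugol photograph is opened. The reader then records a second result, D-VIA plus Lugol, reported as exploratory.

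A display order on the platform is not enough for the distant expert, because photographs may also travel by e-mail, MMS or the RAFT network. Whatever the channel, the Lugol photograph should be released only once the first result is recorded.

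Two statements should be added. The protocol should say whether the on-site expert's live VIA comes before or after Lugol, which settles comparisons 2 and 5. The sponsor should also state which of the two distant results goes back to the health worker for the consensus discussion; this review does not propose one.

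The cost is one extra field on the reading form and staged release of one photograph, with no added women or examinations. The D-VIA figures may be less favourable than with the Lugol picture.

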Cervical cancer is the second most prevalent cancer in women Worldwide ([1](#_ENREF_1)). In Madagascar, there are about 1553 new cancer cases every year ([2](#_ENREF_2)) and, according to country statistics ([3](#_ENREF_3)), 1085 women died in 2010, which makes cervical cancer a leading cause of cancer death in females. In Western Countries, most of cervical cancer can be prevented through cytology-based or HPV screening, but for low-resource countries such as Madagascar, a large-scale screening of precancerous lesions with cytology is hardly possible, because of the lack of specialists and infrastructures.

In order to overcome barriers associated to cytology-based screening programs in low-resource countries, the World Health Organization (WHO) has recommended the use of visual inspection with acetic acid (VIA), since it is a low cost method, easy to perform and does not need specialized laboratory. Additionally, VIA allows reducing the time between when testing occurs and results are available, which allows women to be screened and treated in a single appointment (“see-and-treat approach”).

On the other side, a major drawback of VIA is subjectivity and reliability because of lack of training and expertise. The effectiveness of VIA as screening tool depends essentially from the training of the healthcare workers for diagnosis, appropriate referral and treatment of cervical pre-cancer and cancer in women living in rural Africa with limited access to care. Because the training determines the effectiveness of the VIA, it highlights the potential advantage to develop a strategy for facilitating training and supervision for novice healthcare professional working in areas where physicians are not available.

Digital imaging may offer a support for physician, but problems are that it needs digital cameras, which are expensive and require substantial field training to operate. New Smartphones appear to be an obvious choice for the development of these "next-generation" tools for digital image acquisition. Potential advantage of Smartphones is that it is “easy-use” device, allows immediate image capture and transmissions to expert via MMS in a real time for advice.

Mobile telemedicine is a very promising tool for cervical cancer screening in these countries. In view of growing applicability of this technology we will examine the feasibility, reliability and validity of a Smartphone for pre-cancer detection in low-resource countries.

1. **Objective**

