***Statistical analysis:***

Sample size: Based on previous studies in Ambanja (population of 28,468), Madagascar, we assume that the prevalence of CIN2+ lesions detected by D-VIA will be of 8% and of 4% by classical VIA interpretation. We have assumed 80% power at an alpha level of 0.05, using a 2-sided hypothesis. With this assumption, 1000 women will be needed.

Adequacy results: VIA and D-VIA results will be categorized as “satisfactory” (positive or negative) and “unsatisfactory”. Adequacy results (satisfactory or unsatisfactory) will be compared. Comparisons of percentages will be made between positive and negative VIA and positive and negative D-VIA. The McNemar’s test for comparisons and the Cohen’s kappa coefficient to measure reproducibility between VIA and D-VIA will be used.

Agreement results: Percentage of agreement will be calculated for each pair of on-site results and for distant D-VIA results by using McNemar’s test and adjust the p values with Bonferroni correction for multiple comparisons in order to overcorrect for Type I errors. Agreement of results will be also evaluated using Cohen’s kappa coefficient.

The following agreement results between assessors will be determined:

1) VIA results made by on-site health worker vs. distant expert D-VIA results

2) VIA results made by on-site expert vs. distant expert D-VIA results

3) VIA results made by on-site health worker vs. VIA results made by on-site expert

4) VIA results made by on-site health worker vs. on-site health worker’s D-VIA blinded results at 3 months

5) VIA results made by on-site expert vs. on-site expert D-VIA blinded results at 3 months

6) On-site health worker’s D-VIA blinded results at 3 months vs. on-site expert D-VIA blinded results at 3 months

7) On-site health worker’s D-VIA blinded results at 3 months vs. distant expert D-VIA results

8) On-site expert D-VIA blinded results at 3 months vs. distant expert D-VIA results

Accuracy: Sensitivities and specificities for the gold standard (cervical histology) will be obtained with the Smartphone diagnosis. Positive and negative predictive values will also be determined.

1. **Expected contribution**

Smartphone high-quality photographic technology has proven to be very useful in detecting pre- cancerous lesions on the cervix in a previous study that also took place in Madagascar.

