**VIA -**

**Wait biopsy results**

Negative

Repeat VIA in 5 years

Repeat VIA in 1 year

Negative

VIA + Biopsy

Quality control

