**E-mail**

**MMS**

**HPV positive Women 30-69 years**

Followed by directed & 4-quadrant biopsies & endocervical brushing

By on-site health worker

By on-site expert

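### The lesion-directed part of the histological reference can follow only on-site findings, so the relative sensitivity of D-VIA against VIA is understated by an amount the protocol leaves unmeasured

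*Protocol*

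**What the plan says.** The Protocol, Study procedure, sets the sampling: "Biopsies of the cervix (on the four forties and the lesion if any) and endocervical curettage will be performed". The annex flowchart (5.1) repeats it after the on-site readings: "Followed by directed & 4-quadrant biopsies & endocervical brushing". No restriction to VIA-positive women is stated, and the text of the VIA-negative branch also carries "Wait biopsy results".

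On timing, the Abstract says that the smartphone images are "for later evaluation by a VIA specialist in Geneva linked by telemedicine". Study procedure describes the transfer after the biopsies: "All photographs will be transmitted to University Hospitals of Geneva for expert analysis". It puts the on-site readers' own D-VIA reading three months after the visit.

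On use, the Statistical analysis section says: "Sensitivities and specificities for the gold standard (cervical histology) will be obtained with the Smartphone diagnosis". That sentence names only the smartphone diagnosis. The comparison with conventional VIA comes from the objective in the Abstract and from the sample-size assumption, which is CIN2+ detected in 8% by D-VIA and 4% by VIA.

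**The concern.** A comparison of two tests needs a reference that is equally good at finding disease whichever test is positive. Here a lesion seen on site gets a directed biopsy plus the uniform sampling, while a lesion seen only on the photographs gets the uniform sampling alone. If that sampling misses a CIN2+, the woman is recorded as histology negative. Her D-VIA result then counts as a false positive, and her lesion drops out of the denominator of both sensitivities.

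The second effect helps VIA, because a lesion that VIA missed no longer counts against it. The bias therefore falls on the extra lesions by which the plan expects D-VIA to exceed VIA.

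**Working it through.** **Can a D-VIA reading direct a biopsy?** The three-month readings cannot. The Abstract places the distant reading later than image capture. No step in Study procedure or the flowchart sends a D-VIA finding back to direct or repeat a biopsy. The teleconsultation box leads to diagnosis and management. On the text, the directed specimen follows on-site findings only.

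**Inputs.** From the Statistical analysis section: 8% and 4%, scaled to 1000 women, so 80 and 40 true CIN2+. Assumed, because the Protocol gives no figures:
- every VIA-detected lesion is also seen on D-VIA (nested readings);
- directed biopsy confirms nearly all CIN2+ (taken as 1);
- quadrant plus endocervical sampling detects a fraction q = 0.5 to 0.8, whoever saw the lesion.

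The planned 1000 serves here only as a denominator. As a check, the two-sided comparison of two independent proportions is n = [1.96√(2 × 0.06 × 0.94) + 0.8416√(0.08 × 0.92 + 0.04 × 0.96)]² / 0.04² = 553 per group, or 1106 in total. The paired McNemar formula gives 194 to 587 women for discordance of 0.04 to 0.12. Neither gives 1000, but nothing below depends on it.

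**Formulas**, per 1000 women:
- All specimens: VIA true positives = 40; D-VIA true positives = 40 + 40q.
- Quadrant and endocervical only: VIA = 40q; D-VIA = 80q.
- Apparent VIA sensitivity, among lesions seen by either method = VIA true positives / D-VIA true positives.

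| | Truth | All, q = 0.8 | All, q = 0.5 | Uniform only, q = 0.8 | Uniform only, q = 0.5 |
|---|---|---|---|---|---|
| VIA true positives | 40 | 40 | 40 | 32 | 20 |
| D-VIA true positives | 80 | 72 | 60 | 64 | 40 |
| Ratio D-VIA : VIA | 2.0 | 1.8 | 1.5 | 2.0 | 2.0 |
| Apparent VIA sensitivity | 50% | 56% | 67% | 50% | 50% |
| Absolute gain | 40 | 32 | 20 | 32 | 20 |
| True lesions scored as D-VIA false positives | 0 | 8 | 20 | 16 | 40 |
| True lesions scored as VIA false positives | 0 | 0 | 0 | 8 | 20 |

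The uniform-only reference restores the ratio and the VIA sensitivity. It does not restore the absolute gain, and it adds false positives for both methods.

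**If the readings are not nested.** Take overlap 2%, VIA-only 2%, D-VIA-only 6%, and on-site lesions confirmed with probability 0.95 (all assumed). VIA yield is 0.95 × 4% = 3.8%. D-VIA yield is 0.95 × 2% + 6%q, which is 6.1% at q = 0.7 and 4.9% at q = 0.5. The ratios are 6.1/3.8 = 1.61 and 4.9/3.8 = 1.29, against 2.0 in truth. Nesting is the milder case.

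**Specificity.** The 8 to 20 misclassified women fall among 1000 − 72 = 928 to 1000 − 60 = 940 women recorded as free of CIN2+. The loss for D-VIA is at most 8/928 = 0.9 to 20/940 = 2.1 percentage points.

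**The case against.** **The reference is mainly uniform.** A reader might infer that histology as a whole is targeted by on-site VIA, or that only VIA-positive women are verified. The documents do not support that: quadrant and endocervical sampling carries no VIA restriction. What remains is the asymmetry from one added specimen.

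**The timing is inferred.** Study procedure is not strictly chronological, since the smear and the same-visit treatment are listed after the three-month reading. The Introduction says that a smartphone "allows immediate image capture and transmissions to expert via MMS in a real time for advice". That sentence describes the potential of the device and is not a study step. The Abstract's wording and the absence of any step from image to biopsy carry the inference, but the Protocol should say so plainly.

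**Nobody is named as defining the lesion.** Two readers examine the woman on site, and Lugol and routine photography are also used. If the university-based expert directs the biopsy, a lesion missed by the health worker but seen by that expert still gets a directed specimen. The asymmetry between health worker and distant expert then shrinks. This stands, and it is a reason to name the reader.

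**The 8% and 4% may already be histology-confirmed yields.** Multiplying by q would then count the loss twice. If they came from similar sampling, the true D-VIA-only yield would be 4/q = 5 to 8 points and the true ratio (4 + 5)/4 = 2.25 to (4 + 8)/4 = 3.0, against 2.0 recorded. The direction is unchanged.

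**The bias is conservative.** This mechanism cannot create a false advantage for D-VIA. That is true, but the size of the difference is still misestimated.

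**Such details belong in an SAP.** This is fair for the sensitivity analysis. It is not fair for specimen labelling, because specimens pooled when taken cannot be separated later.

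**Conclusion.** The point holds as a residual asymmetry. A CIN2+ seen only on D-VIA is less likely to be confirmed than one seen on site, so the relative sensitivity of D-VIA is understated and the sensitivity of VIA inflated. With nested readings, near-complete directed biopsy and an assumed 50% to 80% detection by the uniform sampling, the ratio falls from 2.0 to 1.5-1.8 and apparent VIA sensitivity rises from 50% to 56-67%. The Protocol gives no figure for that detection rate, so the direction is firmer than the size.

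Three stronger readings are not supported:
- VIA is not left untouched, since its sensitivity is flattered.
- The expected gain is not wiped out. With nested readings that would need the uniform sampling to find none of the D-VIA-only lesions.
- A loss of power is not established. With 1000 women, 0.95 confirmation of on-site lesions and q = 0.5, McNemar power is 0.99 if the readings are nested but 0.35 in the non-nested example, and the Protocol does not give the overlap.

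The eight listed agreement comparisons use no histology and are unaffected.

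**What to change.** 1. State in Study procedure whose on-site finding defines the lesion to be biopsied, and that the distant reading does not direct biopsies, if that is the intention.
2. Label and report the directed specimen separately from the quadrant and endocervical specimens. Study procedure names endocervical curettage and the flowchart endocervical brushing. These passages must be reconciled, since this sample is part of the uniform reference.
3. Keep all-specimen histology as the main reference, with a note that its D-VIA v VIA contrast favours on-site VIA.
4. Add a sensitivity analysis of the paired D-VIA v VIA comparison (relative sensitivity) using the quadrant and endocervical specimens only.

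The cost is separate labelling of specimens already planned and one more table, with no added biopsy or reader. The downside is real: the uniform reference counts fewer CIN2+, so intervals are wider and absolute yields lower, and more true lesions are scored as false positives for both methods. It should therefore be read for the relative comparison and not for absolute specificity or PPV. It restores the ratio fully only if the uniform sampling is as likely to find a lesion seen only on D-VIA as one seen on site.

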**5.1 Flowchart**

Learning and improvement of VIA interpretation over time

(Photos used for education purposes)

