**Off site diagnosis**

**On site diagnosis**

**TELECONSULTATION**

**DIAGNOSIS CONSENSUS AND MANAGEMENT**

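### The health worker's three-month re-reading is masked only to the worker's own first result, after the distant diagnosis has been fed back, so comparison 7 is not independent and is probably biased upward

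*Protocol*

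**What the plan says.** The protocol's Study procedure fixes the following sequence.

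- The health worker performs conventional VIA. A university-based on-site expert does a second VIA, explicitly blinded to the health worker's result.
- Photographs go to Geneva for expert reading. Then: "The “offsite” diagnosis will be transmitted to health care worker having conducted the “in-site” diagnosis and consensus will be discussed". The flowchart shows the same step, with on-site and off-site diagnoses leading to "DIAGNOSIS CONSENSUS AND MANAGEMENT".
- The on-site health worker and the on-site expert "will evaluate the stored digital images (D-VIA) three months after the initial visit, and blinded to their original evaluation".

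Images are stored on the online platform, which the same section describes when it introduces the questionnaires: "These questionnaires will be available in a secured online platform containing all data from all participants". The flowchart also routes women according to biopsy results.

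Under Statistical analysis, the three-month readings are called blinded and enter comparisons 4 to 8. Comparison 7 is "On-site health worker’s D-VIA blinded results at 3 months vs. distant expert D-VIA results". Agreement is assessed by percentage agreement, McNemar's test with Bonferroni adjustment, and Cohen's kappa. The flowchart also carries the label "Learning and improvement of VIA interpretation over time", and Study design places recruitment in July 2014.

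**The concern.** An agreement study needs the two readings being compared to be made without knowledge of each other. Here one of the two is disclosed to the other reader and discussed before that reader looks at the same images again. The stated masking covers only the reader's own first result, which is not the result that matters for comparison 7.

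Comparison 7 would be read as evidence that a local health worker interprets smartphone photographs much as a distant expert does. If part of the agreement comes from recall of the distant diagnosis or from seeing it in the record, that conclusion is too favourable. A later analysis plan cannot restore the masking once the readings have been made, so the protocol is the place to settle it.

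**Working it through.** **Inputs.** The protocol gives no expected kappa and no estimate of recall, so there is no planned figure to reproduce on this point; the sample size of 1000 does not enter. The true kappa and the share r of re-readings that follow the known distant diagnosis are assumptions. The positive rates of 8% (D-VIA) and 4% (VIA) are the sample-size assumptions for CIN2+ detection, borrowed here as illustrative positive rates.

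**Comparison 7, equal positive rates.** Let Po be observed agreement and Pe chance agreement. If a share r of re-readings copies the distant result regardless of what that result is, then Po′ = r + (1 − r)Po and Pe is unchanged, so

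kappa′ = (Po′ − Pe)/(1 − Pe) = r + (1 − r) × kappa.

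Check at 8% positive for both readers, true kappa 0.40:
- Pe = 0.08² + 0.92² = 0.8528
- Po = 0.8528 + 0.40 × 0.1472 = 0.9117

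| r | Po′ | kappa′ |
|---|---|---|
| 0 | 0.912 | 0.40 |
| 0.1 | 0.921 | 0.1 + 0.9 × 0.40 = 0.46 |
| 0.2 | 0.929 | 0.2 + 0.8 × 0.40 = 0.52 |

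Other assumed values show the same pattern. A true kappa of 0.30 becomes 0.37 at r = 0.1 and 0.475 at r = 0.25; a true kappa of 0.50 becomes 0.55 and 0.625.

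**Comparison 7, unequal positive rates.** With 8% for the distant expert and 4% for the worker, a true kappa of 0.30 becomes 0.39 at r = 0.1 and 0.51 at r = 0.25. The worker's positive rate also moves toward the expert's. At r = 0.1 it is 0.1 × 8% + 0.9 × 4% = 4.4%, so the 4-point gap that McNemar's test would examine shrinks to 3.6 points.

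**Comparison 4 (worker's VIA v own re-reading).** With equal positive rates,

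kappa′ = (1 − r) × kappa_self + r × kappa_distant,

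where kappa_self is the worker's agreement with their own VIA without feedback and kappa_distant is the agreement of that VIA with the distant expert. With assumed values 0.70 and 0.40 and r = 0.25: 0.75 × 0.70 + 0.25 × 0.40 = 0.625. Here self-agreement falls. It would rise only if the worker's VIA agreed better with the distant expert than with the worker's own unaided re-reading.

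**Remaining comparisons.**
- Comparison 6 (worker's v on-site expert's re-reading) has no fixed direction. It depends on how close the on-site expert is to the distant expert.
- Comparisons 5 and 8 use the on-site expert's re-reading. The text names only the health worker as recipient of the feedback, so an effect is possible but not shown.
- Comparisons 1 to 3 use no re-readings. As Study procedure is ordered, each woman's VIA precedes feedback on her photographs, so the health worker's VIA in 1 and 3 is exposed only to learning carried over from earlier women.

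**The case against.** **Silence is not unmasking.** No section says that re-readers see the distant diagnosis, consensus or biopsy results while reading, and the sentence about the platform concerns where questionnaires are held. This stands for histology and record access, which cannot be shown from the text. It does not stand for the distant diagnosis, which the protocol says is given to the worker. Where the protocol wants masking between readers, as for the on-site expert's first VIA, it says so.

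**Recall may be weak.** Three months, about three photographs per woman and 1000 women make extensive recall unlikely. This is fair, and it is why small values of r are the ones to look at. Even r = 0.1 moves an assumed kappa of 0.40 to 0.46.

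**A reader might infer that agreement is inflated throughout.** The documents do not support that: only comparison 7 has an expected direction, and comparison 4 can fall.

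**A reader might infer that the VIA comparator drifts during accrual.** Recruitment lasts one month and feedback turnaround is not fixed. Real-time advice appears in the Introduction as a potential advantage of smartphones, not as a procedure. The flowchart label on learning is followed by a note that photographs serve education, which Study procedure places later. Drift is possible, not shown.

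**A reader might infer that primary outcome 2 is compromised because improvement over time is averaged away.** That outcome asks how the distant expert may improve VIA results and mentions no time trend.

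**Scope.** Agreement is a secondary outcome, and the distant expert's own D-VIA accuracy does not use the re-readings. Both points are correct and limit the weight of the problem.

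**Conclusion.** The point holds for comparison 7. The protocol discloses and discusses the distant diagnosis with the health worker, then treats that worker's later reading of the same images as blinded when it is masked only to the worker's own first result. The comparison is not independent and is probably biased upward. The size is unknown: 0.06 to 0.12 on the kappa scale if the true kappa is 0.40 and 10% to 20% of re-readings follow the known diagnosis, all of these being assumed values. Comparisons 4 and 6 are also affected, without a fixed direction. It is a correctable weakness in a secondary analysis and should be fixed before the readings are made.

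**What to change.** 1. **Study procedure.** State that the three-month readings use de-identified, renumbered images in random order, without access to the platform record, and that readers are masked to the distant diagnosis, the consensus and histology as well as to their own first result.
2. **Statistical analysis.** State that comparisons 4, 6 and 7 follow feedback to the health worker and are not fully independent of it. Renumbering and random order reduce recall; they cannot remove what the worker has learned.
3. **Sensitivity table.** Show comparisons 1 and 3 by recruitment order, for example first v second half, to reveal any change in the worker's VIA across women during July 2014. This stays a sensitivity analysis and does not redefine primary outcome 2.

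The cost is a small image export with renumbering and one extra table. No additional reader or patient procedure is needed.
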